### Missing data and intervention adherence

The occurrence of missing data will be reported for each questionnaire and study time point. Participant intervention adherence, planned absences and study dropouts will be recorded and reported. When possible the causes for missing data, absences or dropout will be reported. Families that miss sessions will be caught up over the phone or conference call before the next session.

### Adverse events

Adverse events will be recorded.

### Statistical analysis

The primary outcome measure (SCP questionnaire)
^16^ will be analysed using visual analysis and multi-level modelling to track individual participant changes over 9 months from baseline to follow up
^39^.

The secondary outcome measures will be analysed for pre-post differences. Data will be analysed using SPSS version 22 statistical software. It is likely that we will be underpowered to detect any significant statistical differences between the pre and post intervention scores; therefore effect sizes (Cohen’s d) will also be calculated. The parent, teacher and adolescent responses to the questionnaires will also be compared to investigate the consistencies between different informants.

We anticipate that adolescent informants will report the greatest positive changes compared to other informants. We also anticipate that the adolescents will report greater improvements on the social knowledge on the TASSK, than on the social performance on the SCP or SDQ (prosocial or peer scale) and social cognition on the SASI. We also expect to see secondary improvements on adolescent self-reports of anxiety on the BAI raw score, social anxiety on the SWS raw total score and self-esteem on the RSE raw total score. We expect to see an increase in camouflaging on the CAT-Q on all the subscales.

In line with previous social skills intervention research we anticipate that positive changes in social performance will be noted by the parents, but that schoolteachers will not observe a change post intervention on the SRS, SDQ and SWS. Specifically we expect parents to report improvements in the SWS total raw score, as well as improvements on the SDQ raw prosocial scale and peer difficulties scale, and improvements on the SRS social communication scale and repetitive and ritualised behaviours scale.

The acceptability of the intervention to families will be assessed using the IAQ. Descriptive statistics will be used to summarise the responses alongside a qualitative summary of the open text answers. We expect that most families will report having positive experiences of the PEERS programme. Based on previous randomised controlled trials we predict that adherence will be on average 80% and that up to two participating families may dropout (Laugeson
*et al.,* 2015; Schohl
*et al.,* 2014).

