### Study design

We will be employing an uncontrolled trial design. To maximise the clinical reliability of the trial we will use a systematic multiple-case series design with case tracking. We aim to recruit participants with a similar degree of social impairment, and intellectual ability.

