### Sample size

A sample size of 6–10 girls and their parents will be invited to take part in the study - this is the group size recommended by the PEERS intervention manual. At present the effect size for this intervention in girls with TS is unknown. This pilot will serve as the basis to estimate the intervention’s effect size and sample size for a future randomised control trial.

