### Study centres/Recruitment

Participants will be recruited from the
*Social Skills and Relationships in Turner Syndrome Study* (SOAR), which recruits children and young women with TS from the Turner Syndrome Support Society, the NHS Great Ormond Street Hospital and the NHS University College London Hospitals. 

The SOAR study is conducting online mental health and social cognition questionnaires with 200 girls and young women with TS and their parents. A subset of families from this large cohort that meet the trial’s inclusion criteria will be invited to take part in the intervention study.

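### Adding plain Cohen's d does not answer low power with 6–10 girls: on n−1 df it overstates the effect by about 9–19% on average, and a point value hides the imprecision (minor)

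*Protocol article*

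**What the plan says.** All references are to the protocol article.

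- **Sample size:** "A sample size of 6–10 girls and their parents will be invited to take part in the study". The reason given is that "this is the group size recommended by the PEERS intervention manual", and the article adds that "At present the effect size for this intervention in girls with TS is unknown".
- **Statistical analysis, secondary outcomes:** "The secondary outcome measures will be analysed for pre-post differences". The section then says these comparisons will probably be underpowered and continues: "therefore effect sizes (Cohen’s d) will also be calculated". No standardiser, small-sample correction or interval is named.
- **Statistical analysis, primary outcome:** the SCP is assigned visual inspection and a multi-level model. Cohen's d is not mentioned for it.
- **Statistical analysis, dropout:** a loss of as many as two families is foreseen.
- **Study design:** "We aim to recruit participants with a similar degree of social impairment, and intellectual ability".
- **Screening assessments and Secondary outcome measures:** a poor score on the SDQ peer scale is a route to eligibility. The SDQ is also a secondary outcome, and the Statistical analysis section predicts parent-reported improvement on that scale.

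**The concern.** The article names an estimator as its response to a problem it admits. At these sample sizes the estimator has two weaknesses.

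First, d divides a mean change by an SD estimated from very few girls. The expectation of one over a small-sample SD exceeds one over the true SD, so d is too large on average.

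Second, d is no more precise than the test it supplements. Given alone, it offers a number where the honest message is a wide range.

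At stake is how the secondary results of a first pilot in this population will be read. They would look somewhat larger, and a good deal firmer, than six to ten girls can support.

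**Working it through.** The article states no alpha, power, SD or effect size, and the sample size is a manual's group size. There is therefore no figure in the plan to reproduce.

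**Inputs.** n = 6 to 10 (Sample size). Up to two families lost (Statistical analysis), so the smallest number of completers is 6 − 2 = 4 and the largest allowing for that loss is 10 − 2 = 8. Normal scores are assumed.

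**Step 1: bias with n−1 df.** This applies when d uses the SD of change or the baseline SD. The expected value of d is the true value divided by J, where J(df) = Γ(df/2) / [√(df/2) · Γ((df−1)/2)]. The overstatement is 1/J − 1.

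- n=6: J(5) = Γ(2.5) / [√2.5 · Γ(2)] = 1.3293 / 1.5811 = 0.841
- n=4: J(3) = Γ(1.5) / [√1.5 · Γ(1)] = 0.8862 / 1.2247 = 0.724

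| n | J | Overstatement | A true 0.50 reads on average |
|---|---|---|---|
| 10 | 0.914 | 9.4% | 0.55 |
| 8 | 0.888 | 12.6% | 0.56 |
| 6 | 0.841 | 18.9% | 0.59 |
| 4 | 0.724 | 38.2% | 0.69 |

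Simulation with 400,000 replicates per setting agrees: about 9.5%, 12.7%, 19.1% and 38–39%.

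**Step 2: bias with a pooled or average pre/post SD.** The approximate df is 2(n−1)/(1+r²), where r is the pre/post correlation. The article gives no r, so a range is assumed.

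| r | n=10 | n=6 | n=4 |
|---|---|---|---|
| 0 | 4.4% | 8.4% | 15.1% |
| 0.5 | 5.6% | 10.8% | 19.9% |
| 0.8 | 7.6% | 14.8% | 28.6% |

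Simulation gives slightly lower values, for example 13.8% at n=6 and r=0.8. For 6 to 10 girls the range is roughly 4–15%.

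**Step 3: imprecision.** For a paired d on the SD of change, t = d√n. The 95% limits are the noncentrality values that place t at the 97.5th and 2.5th percentiles of the noncentral t distribution, divided by √n. For an observed d of 0.5:

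- n=10: t = 1.58, CI −0.17 to 1.15 (width 1.32)
- n=6: t = 1.22, CI −0.38 to 1.33 (width 1.71)
- n=4: t = 1.00, CI −0.58 to 1.52 (width 2.10)

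Against these widths, the average bias in a true d of 0.5 is about 0.05 (n=10) to 0.09 (n=6).

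**Step 4: selection, illustration only.** Suppose selection cut the SD of the selected trait to u = 0.8 of its value. An outcome correlated ρ with that trait keeps √(1 − ρ²(1 − u²)) of its baseline SD.

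- ρ=1: 0.80, so a baseline-SD d rises by 25%
- ρ=0.5: √0.91 = 0.954, a rise of 4.8%
- ρ=0: no change

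For the SD of change, with baseline itself restricted to 0.8, the ratio is √{[(1−r)²u² + 1 − r²] / (2 − 2r)}. This is 0.95 at r=0.5 and 0.98 at r=0.8. The value u=0.8 is assumed, because the article gives neither a cut-off nor a restricted SD.

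**The case against.** The strongest objection is that this rests on silence. A condensed article need not state the correction, standardiser or interval, and an analysis plan that is not shown may contain them. That stands for the interval and the standardiser taken alone. It has less force for the estimator, because the article names Cohen's d and offers it as the response to low power.

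It is also true that the pre-post analysis stays, that d is an addition, and that the article is frank about power. The bias is small beside the sampling error, d attaches only to secondary outcomes, and the study's main aims are piloting, feasibility and acceptability. All of this limits the weight of the point.

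Four stronger readings are tempting, and the documents do not support them.

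- **That selection has shrunk the SD.** The Study design section states an aim only, and no standardiser is named. The effect could matter for a baseline SD on a scale close to the criteria, notably the SDQ peer scale. It would be much weaker for the SD of change. A large inflation factor would require an assumed cut-off that the article does not give.
- **That informants or instruments will be ranked on d.** The Statistical analysis section says informants' responses will be compared, and several predictions name raw scores. The prediction that knowledge gains will exceed performance and social cognition gains may need a common metric, but d is not specified for it.
- **That the SOAR cohort offers the right SD.** The article says "The SOAR study is conducting online mental health and social cognition questionnaires with 200 girls and young women with TS and their parents". An SD from that broader cohort answers a different question from the SD that a trial in similarly selected girls would meet. Restricted to ages 16–20, it would also no longer rest on 200 girls.
- **That this d will size the next trial.** The article says "This pilot will serve as the basis to estimate the intervention’s effect size and sample size for a future randomised control trial", but does not say which outcome or estimator will be used.

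**Conclusion.** The point holds as a minor one. Plain Cohen's d at the planned size overstates the effect on average by about 9% (n=10) to 19% (n=6) on n−1 df, and by 38% at four completers. That last figure needs both the smallest recruitment and the largest foreseen dropout. With a pooled or average pre/post SD the range for n=10 to 6 is roughly 4–15%, taking r between 0 and 0.8. These figures assume normal scores and that no correction is specified elsewhere.

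Imprecision matters more than bias: the intervals around an observed 0.5 include zero at every size considered. Any further inflation through selection is possible for a baseline SD, but it cannot be quantified from the article.

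**What to change.** In the Statistical analysis section, replace Cohen's d with Hedges' g (d multiplied by J for the df of the chosen standardiser). Name the standardiser and give a 95% CI. Report it beside the raw mean change with its own 95% CI. State that informants will be compared on raw change on the same scale.

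Standardising by a SOAR cohort SD for the same scale and informant is at most an optional sensitivity display, labelled as referring to a broader population.

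The cost is a sentence of wording and a few lines of calculation. On n−1 df the reported effects shrink by about 9% at n=10 (1 − 0.914) to 16% at n=6 (1 − 0.841), so an observed 0.50 becomes 0.46 or 0.42. They will also look visibly imprecise. The correction removes the average bias but does not narrow the interval or steady a noisy denominator.

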## Ethics and dissemination

### Ethics and consent

All participants (young people aged 16–20 and their parent) will give written informed consent prior to entry to the SOAR study. The study has been approved by the West London GTAC Ethics Committee (IRAS: 219817).

### Dissemination

The results of the study will be disseminated at the Turner Syndrome Support Society conference, the study website, at international research conferences and in research articles published in peer-reviewed journals.

## Discussion

This is the first study to pilot a social skills training program with adolescents and young women with TS. Given the PEERS program’s success with teenagers on the spectrum, it is anticipated that young women with TS will also benefit from taking part.

This pilot study has been designed to take an approach of high internal validity. This approach is appropriate given that it is a feasibility pilot conducted with a small number of participants (n=6–10), however the disadvantage of the approach is that the study has low external validity, which reduces the generalizability of the findings. This study will need to be replicated with young people with different social skills profiles, intellectual ability and hormone treatment status.

To our knowledge this will also be the first trial of PEERS delivered online and offline. TS is a rare genetic disorder and the delivery of the full program face to face would have resulted in many families being excluded due to geographical constraints. The program’s acceptability to families will be assessed and this feedback will be used to inform future replications of the intervention. Should the combination of online and offline prove successful, this will enable the to program to be made more widely available.

When assessing social skills it is important to employ a range of assessment tools, which assess different domains of social skills (social knowledge, performance and cognition), as well as a variety of informants
^40,
41^. Meta-analyses of social skills intervention studies show that parents and young people report changes in social skills after taking part in social skills interventions. However, these improvements are rarely reported by teachers
^41,
42^. There is a trend for young people to overestimate the changes in their social skills compared to other informants
^41,
42^. However, a recent meta-analysis of the young person self-report measures suggests that the improvements relate to changes in their social knowledge rather than their social performance
^41^.

The assessment battery has been designed to measure changes in social skills, in the domains of social performance, social knowledge and social cognition. These outcomes will be reported on by the parents, teachers and the young people themselves. Teachers and parents will be asked to report on changes in social performance through questionnaires. The young people will complete questionnaires which measure social performance and social knowledge, as well as an online task to measure changes in social cognition. The maintenance of any potential treatment gains in social performance will be assessed by the parent report at a 3 month follow-up.

It is likely that the adolescent and parent reports will be prone to expectancy biases
^43^. They may exaggerate treatment effects due to their investment in taking part in the intervention. Using external observers (such as teachers or blinded study administrative assessors) is essential to help understand these biases and assess whether changes in performance generalise to other settings
^41,
44^. Unfortunately, due to the small scale of this project, assessments by external observers will not be feasible.

Meta-analyses of social skills interventions for children on the autistic spectrum using the SRS have shown that the largest treatment gains are made in the social communication and repetitive and ritualised behaviours scale
^21^. The changes in repetitive and ritualised behaviours may be mediated by reductions in anxiety or increases in social awareness
^21,
45^. The majority of the participants included in the meta-analyses were adolescent males, therefore it remains to be seen whether these patterns of improvement will be replicated in females with TS.

This study will also use a novel measure of social camouflaging
^46^. Social camouflaging is a strategy adopted by people on the spectrum to manage social situations. It has been likened to wearing a ‘social mask’, where the individual puts on ‘their best self’
^46^. Camouflaging typically involves masking and compensating for social deficits
^46–
48^. This might involve consciously performing a range of non-verbal cues such as making eye contact during conversations and imitating facial expressions and gestures, or following learnt social scripts such as using pre-prepared jokes or comments
^49^. Recent research suggests that females are better at camouflaging than males
^48,
50^. We anticipate that the intervention will help the participants become more aware of their camouflaging and help them to camouflage more effectively if they choose to use it as a strategy.

## Conclusion

This will be the first social skills training programme trialled with adolescents and young women with TS. Should the trial prove successful, the initial results will be used to inform the sample size for a future randomised controlled trial. Additionally, neither research trials using the PEERS program exclusively in girls, nor trials delivering PEERS online have been published. Therefore, this trial may have a broader impact on the development of treatment strategies for both for young women that experience social skills difficulties (including those on the autistic spectrum), but also for broadening access to treatment by using technology.

## Data availability

No data are associated with the article.
